### Economic evaluation

Active implementation entails an additional cost that may or may not be offset by health gains and/or reductions in health service utilisation. Evidence is limited regarding this trade-off between incremental costs (savings) and effects for active implementation versus simple dissemination of practice guidelines for management of LBP. Hoeijenbos *et al*. [87] conducted a cost-utility analysis comparing standard dissemination versus active implementation of the Royal Dutch Physiotherapy Association (RDPA) guideline for non-specific LBP based on data from the Bekkering CRT [40,41]. While lower per patient healthcare utilisation in the active implementation group (mean = EUR 125, SD = EUR 91 versus mean = EUR 145, SD = EUR 95, p = 0.026) offset the relatively modest incremental treatment cost of active implementation (EUR 366 per physiotherapist), the observed differences in healthcare utilisation (and health outcomes) could not be attributed to an intervention effect due to failure to control for pre-existing between-group differences in patient characteristics. Hoeijenbos *et al*. [87] therefore concluded that 'it is very likely that the extended implementation strategy incurs extra costs without producing health gains, hence it is very likely to be not cost-effective.'

The implementation strategy employed by Bekkering *et al*. [40,41] and the RDPA guideline differ from the ALIGN intervention and the NHMRC guideline. Importantly, the RDPA guideline contains no specific recommendation that would limit referral for imaging [88], and the implementation strategy employed by Bekkering *et al*. [40,41] made no attempt to target referral behaviour for imaging. Another recently completed study [33,89] will shortly report on the cost-effectiveness of active implementation versus standard dissemination of the NHMRC guideline, but its findings will relate to general practice rather than to the allied health setting. Findings from the economic evaluation described here will therefore complement rather than replicate previous findings.

Economic evaluation alongside the ALIGN CRT will be conducted with the aim of quantifying additional costs (savings) and health gains arising from the ALIGN intervention as compared to access to the guideline via existing practice. Secondary aims will be to determine whether the incremental treatment costs of the ALIGN intervention are offset by reductions in health service expenditure (*i.e*., whether implementing the guideline is cost-saving as compared with existing practice), and to determine whether the ALIGN intervention dominates existing practice (*i.e*., less costly but no less effective). The time horizon for inclusion of relevant costs and consequences for the trial-based evaluation described here coincides with the final scheduled follow-up of patient participants (three months post-onset of their acute LBP episode).

The proposed economic evaluation will take a societal perspective in identifying, measuring, and valuing costs and consequences, but some cost categories likely to produce clinically and economically insignificant variation in incremental cost will be excluded to simplify our analysis [90]. Likewise, we exclude some dimensions of health and HRQoL not captured by the patient-level outcomes and some (but not all) non-health outcomes (*e.g*., social status) on the grounds that their inclusion would be unlikely to be alter policy recommendations. Research and evaluation costs will be excluded except where they might plausibly contribute to a clinically significant treatment effect. Costs common and invariant to both intervention and control groups (*e.g*., costs associated with development and standard dissemination of the guideline) will not be explicitly calculated for the incremental analysis described here.

#### Identification, measurement, and valuation of health outcomes

In line with the main analysis, the primary outcome for the economic analysis will be x-ray referral to three months post-onset of patients' acute LBP episode based on the practitioner checklist. For the economic analysis, we will conduct a secondary analysis under the assumption that referral implies occurrence such that patients will be coded as 'x-ray received' if data from any one of the practitioner completed checklist, clinical file audit, or patient questionnaire indicate x-ray referral or occurrence. Patients will be coded as 'x-ray avoided' if x-ray referral or occurrence is nowhere indicated in data from the practitioner completed checklist, clinical file audit, and patient questionnaire. For the purposes of the economic analysis, x-ray referral and x-ray avoided are intermediate measures of mortality and morbidity effects that occur beyond trial-end arising due to reduced exposure to ionising radiation [91]. Intervention effects with respect to x-ray referral and x-ray avoided to three months post-onset will be estimated using methods specified for the main analysis, controlling for the set of potential confounders specified above.

Additional secondary outcomes for the economic analysis are: any imaging referral (including lumbosacral plain x-ray, full spine plain x-ray, lumbar CT scan, lumbar MRI, or bone scan) and any imaging avoided to three months post-onset, LBP-specific disability at three months post-onset, and HRQoL at three months post-onset. The rationale for measuring referral/avoidance of any imaging in the economic analysis is as described above for the outcome 'imaging referral excluding x-ray.' Intervention effects with respect to any imaging referral/avoidance to three months post-onset will be estimated using methods specified for the main analysis, controlling for the set of potential confounders specified above. LBP-specific disability and HRQoL are included to provide measures of differential health outcomes arising within the trial period due to *inter alia *any between-group difference in providing advice to stay active. Intervention effects with respect to LBP-specific disability will be taken from the main analysis of Roland-Morris Disability Questionnaire (RDQ) at three months post-onset of their acute LBP episode, controlling for the set of potential confounders specified above.

Preference-based HRQoL weights derived from the patient-level AQoL-4D (Assessment of Quality of Life) responses must be combined with a period of time to permit estimation of intervention effects in QALY terms (and incremental cost-effectiveness in cost per QALY terms). Note, however, that follow up of LBP specific disability and HRQoL for the ALIGN study is scheduled for a single time point at three months post-onset. Due to feasibility/resource constraints and to minimise patient attrition at the primary endpoint, we decided not to schedule repeated observations on patient level outcome measures in the present trial. Findings from two studies that informed development of the guideline [92,93] suggest that any intervention effect with respect to pain is likely to arise in the intermediate term (3 to 12 weeks) rather than in the short term (<3 weeks). Based on this limited information as to the time-path of any intervention effect, patients are assumed to transition from their baseline health state to their observed health state (as measured by HRQoL at three months post-onset) at three weeks post-onset, remain stable in their observed health state (as measured by HRQoL at three months post-onset) during the nine weeks from three to twelve weeks post-onset, before transitioning to full or normal health by trial-end. Intervention effects with respect to total QALYs are therefore estimated as the difference between curves for treatment and control groups over the nine weeks from three to twelve weeks post-onset of their acute LBP episode using methods specified for the main analysis of patient level clinical outcome measures and controlling for the set of potential confounders specified above. No attempt has been made to extrapolate from any between-group difference at trial-end based, for example, on secondary data as to the relative stability of pain, disability, and return to work between three and twelve months post-onset [94]. Any between-group differences in transition to chronic lower back pain are therefore excluded from our estimates of incremental effectiveness.

#### Identification, measurement, and valuation of resource use

Incremental costs will reflect resource use associated with development of the implementation intervention, delivery of the implementation strategy, and any changes in clinical practice and subsequent health effects. Methods for the ALIGN cost-analysis will be as described by Mortimer *et al*. [89] for the IMPLEMENT trial (planned analyses) but paid and unpaid costs of homecare will be excluded on the grounds that any between-group variation in homecare costs is expected to be quantitatively unimportant.

Given the characteristic distribution of health costs (truncated at zero and right skewed), the importance of obtaining readily interpretable marginal effects, and our interest in population-average effects, we will model intervention effects on health service expenditure and total costs using one-part GEEs with a log link rather than transformed ordinary least squares or two-part models [95]. Specification of the log link for the GEE model permits natural interpretation of marginal effects on cost without retransformation [95]. Correlation structure, standard errors, and controls for confounding variables will be as specified for the main analysis.

#### Adjustment for differential timing

All costs will be inflated to current AUD for the year of study completion. All costs and benefits will be converted to present values for the year of study completion using an annual discount rate of 5% in the base-case, and annual rates of 3% and 7% in sensitivity analysis.

#### Incremental analysis

Results from the economic evaluation will be expressed as: additional costs (savings) per x-ray referral and per x-ray avoided to three months post-onset; additional costs (savings) per any imaging referral and per any imaging avoided to three months post-onset; additional costs (savings) per point difference in RDQ at three months post-onset; and additional costs (savings) per QALY gained.

#### Uncertainty

Cost-effectiveness acceptability curves (CEACs) will be derived from the joint density of incremental costs (ΔC) and incremental effects (ΔE) for the intervention as compared to existing practice. The joint density will be obtained via non-parametric bootstrapping from the distribution of observed cost/effect pairs for patient participants. Separate CEACs will be derived for upper/lower bound estimates of a pre-specified set of uncertain parameters not estimated with sampling error: development costs (none, full); unit cost for practitioner participant time (AUD 0, average hourly wage rate), unit cost for patient travel/waiting time to attend treatment (AUD 0, average hourly wage rate), and the discount rate (3%, 7%).

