**Methods:**

The design of the study is a cluster randomised trial. Restricted randomisation was used to randomise 210 practices (clusters) to an intervention or control group. Practitioners in the control group received a printed copy of the guideline. Practitioners in the intervention group received a theory-based intervention developed to address prospectively identified barriers to practitioner compliance with the guideline. The intervention primarily consisted of an educational symposium. Patients aged 18 years or older who visit a participating practitioner for acute non-specific LBP of less than three months duration over a two-week data collection period, three months post the intervention symposia, are eligible for inclusion. Sample size calculations are based on recruiting between 15 to 40 patients per practice. Outcome assessors will be blinded to group allocation.

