### Sample size

The primary practitioner outcome is x-ray referral. In our original sample size calculation for this outcome, we estimated that we would require 136 practices (68 physiotherapy and 68 chiropractic practices), each completing checklists for an average of 20 patient participants (providing a total of 2,720 patient participants), to provide 80% power to detect a difference of 10% in x-ray referral between intervention groups. This assumed a 39% x-ray referral rate in the control group, a 5% significance level, and an ICC of 0.10, and allowed for 20% attrition in practices. Empirical research has suggested ICCs of the order of 0.10 for process variables, such as x-ray referral, in primary care [63]. Data on x-ray referral rates were not available for the Australian context, so the x-ray referral rate of 39% was estimated from international research and assumptions regarding the process of x-ray referral in Australia. More specifically, for chiropractors, several international studies have estimated that referral for x-ray for acute LBP ranges from 62% to 72% [17,20,23]. For physiotherapists, we assumed that x-ray referral rates would be similar to those found in Australian general practice, which has been estimated at 28% [64], because many physiotherapists treat patients with LBP on referral from, and in conjunction with, GPs. Because we intended to recruit an equal number of patient participants from physiotherapy and chiropractic practices, we estimated the pooled x-ray referral rate to be 47%. Interventions comparing standard CPG dissemination with no intervention control groups have shown improvements in care of approximately 8% [4]. We therefore anticipated a decrease in the percentage of x-ray referral in the control group of this magnitude, providing an estimated referral rate of 39%.

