#### Primary analyses

We will estimate the effectiveness of the intervention on primary and secondary outcomes with marginal modelling using generalised estimating equations (GEEs). These models will appropriately account for correlation of responses within practice. We plan to fit an exchangeable correlation structure, where responses from the same practice are assumed to be equally correlated [50,72]. Additionally, we intend to use robust variance estimation that will provide valid standard errors even if the within-cluster correlation structure has been incorrectly specified [73,74]. For binary outcomes, a logit link function will be used. In the event that the ICC of an outcome for a particular analysis is negative, we will fit a generalised linear model with no adjustment for clustering (*e.g*., ordinary linear regression), making the assumption that in the context of cluster-based evaluations, negative ICCs are more likely to occur through sampling error than because of a true negative ICC [50].

Our primary analyses of outcomes will include adjustment for stratification variables (professional group and location of the practice) and pre-specified potential confounding variables (Figure 2). The potential confounders have been selected through discussion amongst the investigators and from published research (see Figure 2 notes). All pre-specified confounders will be included in the models even when no baseline imbalance exists. We have chosen this approach because confounder selection strategies that are based on collected data, (*e.g*., selecting confounders using preliminary statistical tests) result in models with poor statistical properties, such as incorrect type I error rates [75-78]. In the circumstance that there is limited data or events (*e.g*., advised bed rest), or both, to adjust for all confounders, we will report estimates of intervention effect from models including only the stratification variables, and baseline of the outcome variables where appropriate (FAB, intention, and behavioural constructs).

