#### Secondary analyses

We will conduct a subgroup analysis to examine whether the effect of the intervention on x-ray referral is modified by professional group (physiotherapist versus chiropractor). We hypothesise that the effect of the intervention may differ by professional group because x-rays are seen as more integral to the treatment of patients for chiropractors compared with physiotherapists [22]. We will examine this by fitting a model that includes an interaction term between intervention group and professional group. The estimated ratio of odds ratios and its 95% CI will be presented from this model.

GEEs will yield unbiased estimates of intervention effect only when data are missing completely at random, or when known covariates that are associated with the missing data mechanism are included in the model (missing at random) [69]. As part of the secondary analyses, we plan to identify potential predictors of missing data through modelling (*e.g*., [81]), and include these predictors in the primary analysis model. We will investigate methods to impute missing outcome data collected at baseline (*e.g*., baseline behavioural constructs, FAB) [82]. Finally, we will investigate methods to adjust for potential differential recruitment [68].

A disadvantage of using GEEs is that only one level of clustering can be modelled. For data collected at the patient level, there are three levels of data: practices, practitioners, and patients. It is possible to allow for clustering at the practice level or the practitioner level. While we have chosen to adjust for clustering at the practice level, because this is the unit of randomisation, there may be an argument for adjusting at the practitioner level if the variation at this level is larger; this could be predicted to arise because the practitioner has a more direct influence on patient outcomes (such as x-ray referral). We will therefore undertake sensitivity analyses investigating the impact of allowing for clustering at the level of the practitioner.

We plan to undertake explanatory analyses to investigate if intervention effects are mediated by our hypothesised predictors of practitioner behaviour [83-85]. Detailed description of our theoretical model and results of these explanatory analyses will form separate publications.

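### The cost-effectiveness acceptability curves are bootstrapped from patients although practices were randomised, so joint cost-effectiveness uncertainty is understated if outcomes correlate within practice

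*Protocol article*

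**What the plan says.** The trial is cluster randomised: "Restricted randomisation was used to randomise 210 practices (clusters) to an intervention or control group" (abstract, Methods). The main models follow that design. Under Primary analyses, outcomes are analysed with generalised estimating equations (GEEs), an exchangeable correlation within practice and robust variance: "These models will appropriately account for correlation of responses within practice". Secondary analyses gives the reason: "While we have chosen to adjust for clustering at the practice level, because this is the unit of randomisation". The resource-use section carries this over to the cost models: "Correlation structure, standard errors, and controls for confounding variables will be as specified for the main analysis".

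The Uncertainty section then derives the CEACs from the joint density of incremental cost (ΔC) and incremental effect (ΔE), and says how that density is obtained: "The joint density will be obtained via non-parametric bootstrapping from the distribution of observed cost/effect pairs for patient participants". Neither that section nor any other mentions drawing practices, a two-stage bootstrap or resampling within strata. The additional CEACs planned there vary only quantities that carry no sampling error (development costs, unit costs of time, discount rate).

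**The concern.** The spread of a bootstrap distribution is set by the unit that is drawn. Keeping a patient's cost and effect together preserves the correlation between the two. It does not preserve the correlation between patients of the same practice. If patients are drawn as independent units, the variance between practices drops out of the joint density. Refitting a practice-clustered GEE in each replicate would not restore it, because the model's standard errors do not enter the bootstrap distribution.

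What is at stake is the probability of cost-effectiveness read from the CEACs. Too narrow a density makes these curves too steep. A probability above 0.5 is shown too high and one below 0.5 too low, so the error can exaggerate a conclusion for or against the intervention.

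**Working it through.** **Inputs from the protocol article.** Sample size: "an ICC of 0.10, and allowed for 20% attrition in practices", an average of 20 patients per practice, 39% x-ray referral in controls, a 10-point difference, 80% power, 5% significance, 136 practices in total. For the trial as recruited: 168 practices completing, taken here as 84 per arm under 1:1 allocation, and an expected 95% interval half-width of ±5% to ±7%.

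**The plan's own figures.** Comparing 39% with 29%, two-sided, with continuity correction, needs 371 patients per arm.
- Design effect = 1 + (20 − 1) × 0.10 = 2.9.
- 371 × 2.9 = 1,075.9 patients per arm; / 20 = 53.8 practices per arm; × 2 = 107.6; / 0.80 = 134.5. This is close to the stated 136. Without continuity correction it is 127.6.
- Half-width for x-ray referral with 84 × 20 = 1,680 patients per arm: 1.96 × √[(0.39 × 0.61 + 0.29 × 0.71) × 2.9 / 1,680] = 5.4 points, inside the stated range.
- The same with patients taken as independent (design effect 1): 3.2 points, below the protocol's own range.

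**Size of the understatement.** With m complete pairs per practice and ICC ρ for net benefit:
- design effect D = 1 + (m − 1)ρ, and the patient-level standard error (SE) is too small by a factor √D;
- actual coverage of a nominal 95% interval = 2Φ(1.96/√D) − 1;
- a CEAC probability that should be p is shown as Φ(√D × Φ⁻¹(p)).

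Only the last row uses planning values from the protocol, and those are for x-ray referral. The other rows are assumptions.

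| ρ | m | D | √D | Coverage | 0.80 shown as |
|---|---|---|---|---|---|
| 0.02 | 10 | 1.18 | 1.09 | 93% | 0.82 |
| 0.05 | 10 | 1.45 | 1.20 | 90% | 0.845 |
| 0.10 | 10 | 1.90 | 1.38 | 84% | 0.88 |
| 0.10 | 20 | 2.90 | 1.70 | 75% | 0.92 |

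By symmetry, a probability that should be 0.20 would be shown as about 0.08 in the last row. The formulas assume equal numbers per practice.

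**Check by simulation.** With 84 practices per arm, 20 patients each, ICC 0.10 and outcome variance 1, the true SE is 0.0588. The patient bootstrap gave 0.0344 and the practice bootstrap 0.0578. Their ratio is 0.595, against 1/√2.9 = 0.587 in theory.

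**Two-stage bootstrap.** Drawing practices and then patients within them, without correction, counts within-practice variance twice. At ρ = 0.02 and m = 10 the variance of a practice mean is 0.02 + 0.98/10 = 0.118. The uncorrected scheme gives 0.118 + 0.098 × 9/10 = 0.206. The SE ratio is √(0.206/0.118) = 1.32, so the SE is about 32% too wide.

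**The case against.** The sentence can be read mildly. It names the distribution drawn from and does not say that patients are drawn without regard to practice; a cluster bootstrap also ends up with patients' pairs. The cost-analysis methods are also referred to a separate paper on the sister general-practice trial, which is not shown. This argues against certainty about what will be done. It does not clear the text, because the only unit named is the patient and nothing in the article replaces it.

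Four stronger readings go beyond the document.
- A reader might infer that the curves use raw, unadjusted differences and so repeat the fault found in an earlier trial's evaluation, whose differences could not be attributed to the intervention "due to failure to control for pre-existing between-group differences in patient characteristics". The article does not say so. The health-outcome and resource-use sections specify confounder-adjusted estimates, and refitting those models in each replicate is compatible with the Uncertainty section. The article simply leaves the refitting unstated.
- A reader might infer that the CEACs are the only inference on cost-effectiveness. Practice-clustered models are planned for cost and for each effect separately. Only the joint uncertainty depends on the bootstrap.
- A reader might take a factor of 1.70 and 75% coverage as the expected size. The ICC of 0.10 is for x-ray referral, and the 20 per practice counts practitioner checklists. Table 1 takes health service use and productivity from the three-month patient questionnaire, which needs separate consent (Recruitment of patient participants). Complete pairs per practice may therefore be fewer.
- A reader might infer a bias in favour of the intervention. The distortion runs in both directions.

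**Conclusion.** The point holds: taken as written, the bootstrap uses the wrong unit for this design and omits between-practice variance from the joint cost-effectiveness uncertainty. This rests on a positive ICC of net benefit, which the protocol assumes for x-ray referral but does not give for cost, quality-adjusted life-years, disability or net benefit. With no such correlation there is no understatement.

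The size is a range. It is small at 10 pairs per practice and ICC 0.02, moderate at ICC 0.05, and large only if the x-ray planning inputs also describe net benefit. Point estimates, both primary outcomes and all GEE intervals are unaffected. According to the Background, patient data collection had only just begun when the article was written, so on that timetable the text could be corrected before any economic result was known.

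**What to change.** In the Uncertainty section, replace the bootstrap sentence with wording to this effect: whole practices are resampled with replacement within arm and randomisation stratum (professional group by location), and all patients of a drawn practice are kept. In each replicate the planned confounder-adjusted cost and effect GEEs are refitted, and the resulting pairs of ΔC and ΔE form the joint density for the CEACs. If a two-stage bootstrap is preferred, specify it with shrinkage correction.

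The cost is a few sentences and a little more computing. No new data are needed. The curves will be flatter, and conclusions about cost-effectiveness correspondingly less certain.
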